# Intranasal fentanyl versus intravenous morphine in the emergency department treatment of severe painful sickle cell crises in children: Study protocol for a randomised controlled trial

**DOI:** 10.1186/1745-6215-13-74

**Published:** 2012-05-30

**Keywords:** Sickle cell disease, Paediatric, Pain, Analgesia, Intranasal, Fentanyl, Randomised Controlled Trial, Double blind

## Abstract

**Background:**

Children with sickle cell disease (SCD) frequently and unpredictably present to the emergency department (ED) with pain. The painful event is the hallmark acute clinical manifestation of SCD, characterised by sudden onset and is usually bony in origin. This study aims to establish if 1.5mcg/kg of intranasal fentanyl (INF; administered via a Mucosal Atomiser Device, MAD™) is non-inferior to intravenous morphine 0.1 mg/kg in severe SCD-associated pain.

**Methods/design:**

This study is a randomised,double-blind, double-dummy active control trial of children (weighing more than 10 kg) between 1 year and 21 years of age with severe painful sickle cell crisis. Severe pain is defined as rated seven or greater on a 0 to 10 age-appropriate numeric pain scale or equivalent. The trial will be conducted in a single tertiary urban paediatric ED in Dublin, Ireland. Each patient will receive a single active agent and a single placebo via the intravenous and intranasal routes. All clinical and research staff, patients and parents will be blinded to the treatment allocation. The primary endpoint is severity of pain scored at 10 min from administration of the study medications. Secondary endpoints include pain severity measured at 0, 5, 15, 20, 30, 60 and 120 min after the administration of analgesia, proportion of patients requiring rescue analgesia and incidence of adverse events. The trial ends at 120 min after the administration of the study drugs. A clinically meaningful difference in validated pain scores has been defined as 13 mm. Setting the permitted threshold to 50% of this limit (6 mm) and assuming both treatments are on average equal, a sample size of 30 patients (15 per group) will provide at least 80% power to demonstrate that INF is non-inferior to IV morphine with a level of significance of 0.05.

**Discussion:**

This clinical trial will inform of the role of INF 1.5mcg/kg via MAD in the acute treatment of severe painful sickle cell crisis in children in the ED setting.

**Trial registration:**

Current Controlled Trials ISRCTN67469672 and EudraCT no. 2011-005161-20

## Background

Children with sickle cell disease (SCD) frequently and unpredictably present to the emergency department (ED) [1]. In these children, pain is a common experience, beginning as early as 4 to 6 months of age [2]. These painful episodes (often referred to as a pain “crisis”) are the hallmark acute clinical manifestation of SCD, characterised by the sudden onset of pain. Although pain is a dominant feature in the medical lives of children with SCD, with approximately 70% of their hospitalisations after ED presentation being for uncontrolled pain [1-3], it is often under-recognised and undertreated [4-6]. Unrelieved pain does not only have negative consequences, such as missed days of school, restriction of other activities, and fear or mistrust of health care providers, but also can lead to amplified responses to subsequent pain experiences and sensitivity to pain later in life [2,7]. Furthermore, frequent painful episodes are associated with early mortality in patients with SCD [3,8].

Suboptimal acute pain management in SCD patients is associated with caregivers' preoccupation with the pathophysiological causes of vaso-occlusion and concern of creating opioid dependence [9], and a negative attitude toward patients with SCD in urban hospitals and EDs [5,9-11]. The truth regarding opiate addiction in patients with SCD is markedly less dramatic than conventional opinion would suggest. Prevalence estimates for opiate addiction among patients with SCD range from 0.5% to 8% compared to patients with other chronic pain syndromes with opiate addition rates of 3% to 16% [9,12,13]. Two putative biological mechanisms may explain the relatively low prevalence of opiate addiction among SCD patients. First, the allelic variants in the genes involving the opioid (UGT2B7, OPRM1, and ABCB1 genes) and non-opioid system (COMT gene) can alter the efficacy of morphine in SCD patients [14,15]. Second, the pharmacokinetics of morphine is altered in SCD patients, with clearance of morphine being 3–10 fold higher in SCD patients compared with healthy non-SCD patients [16].

Although treating acute painful sickle cell crisis (PSCC) with appropriate potent analgesia [intravenous (IV) and/or oral controlled-release morphine] is humane and reduces the length of hospitalisation in SCD patients with mild to moderate pain [17], the evidence base for acute ED pain management in children with PSCC is limited [18]. Alternative, quicker and pain-free methods of providing safe and effective analgesia include the intranasal (IN) route for the administration of opiates such as fentanyl, sufentanil and diamorphine [19-35]. The IN route is increasingly being used for the safe administration of analgesia in paediatric patients with painful conditions (e.g. burns, long bone fractures and post-operatively) [24,26,28,34,35]. In the emergency care setting, IN fentanyl is also currently used for managing pain in children in the pre-hospital setting [36,37]. Compared with other routes of drug administration, the IN route has unique advantages that may allow for more efficient use of resources, more rapid pain relief, and higher patient and provider satisfaction [38,39]. The highly vascularised nasal mucosa and the olfactory tissue in direct contact with the central nervous system permit rapid drug absorption, high bioavailability and onset of action comparable with IV drug administration [39]. Furthermore, IN drug administration is also relatively painless, inexpensive, convenient and easy to deliver with minimal training [39]. Fentanyl is a potent opioid (approximately 100 times more potent than morphine) with high bioavailability and a short duration of action (IN fentanyl plasma half-life of 1 h). When used in analgesic doses, fentanyl results in minimal sedation and little haemodynamic instability [40].

The primary aim of this study is to determine if 1.5mcg/kg of intranasal fentanyl via a Mucosal Atomiser Device (MAD™) is non-inferior to intravenous morphine in children presenting with severe pain associated with SCD.

## Methods/design

### Study aims

To determine whether 1.5mcg/kg IN fentanyl is non-inferior to 0.1 mg/kg IV morphine in the management of severe pain in children with PSCC.

### Study design and setting

This is a randomised, double-blind, double-dummy, active control clinical trial. It will be conducted at a single tertiary urban paediatric ED (Our Lady’s Children’s Hospital Crumlin (OLCHC)) in Dublin, Ireland.

### Subject selection

Children satisfying the screening inclusion and exclusion criteria, and the randomisation inclusion and exclusion criteria (Table 1), who present to the recruiting ED during the study period will be eligible for recruitment into the trial.

**Table 1 T1:** Inclusion and exclusion criteria

*Inclusion criteria*:	
·	Ages 1 – 21 years
·	≥10 kg and ≤70 kg
·	Known sickle cell disease presenting with severe pain
·	Written informed consent, ideally from both parents (and assent, where appropriate), obtained prior to painful crisis (for example, in Haematology clinic)
·	Verbal consent (and assent, where appropriate) obtained at the time of the painful crisis in the ED
·	Hospital admission required for painful crisis
*Exclusion Criteria:*	
·	Patient has received parenteral narcotic analgesic within 4 hours of ED presentation
·	Oxygen saturations below 95% on initial assessment
·	Altered conscious state as defined by a Glasgow Coma score less than 15
·	Contraindications to fentanyl/morphine usage
·	Inability to secure IV access
·	Patient has participated in another clinical trial involving an Investigation Medicinal Product (IMP) within 4 weeks of dosing, or is currently enrolled in another clinical trial involving an IMP, or has been previously enrolled in this trial
·	Patients who have any condition that would make him/her, in the opinion of the Investigator or Sponsor, unsuitable for the study, or who are, in the opinion of the Investigator, not likely to complete the study for any reason
·	Blocked or traumatised nose

### Definition of painful crisis

An episode of severe pain is defined as the occurrence of pain in the extremities, back, abdomen or chest due to sickle-cell disease that is rated 7 or greater on a 0–10 numeric pain scale or equivalent [8].

### Inclusion and exclusion criteria

Inclusion and exclusion criteria are presented in Table 1.

### Patient randomisation

Patients who fulfil the randomisation eligibility criteria and whose parents provide informed consent will be randomised to receive intranasal fentanyl and intravenous placebo or intranasal placebo or intravenous morphine. The randomisation process was designed by CSTAR (Health Research Board Centre for Support and Training in Analysis and Research). Trial randomisation codes will be generated by CSTAR. The randomisation process provides a random allocation of 30 subjects between the two treatment groups. Randomisation will be on an individual basis using a computer-generated block randomisation. The randomisation is not stratified.

### Randomisation treatments

All study drugs will be packaged in blinded trial packs by a clinical trial pharmacist who is blinded to interventions and outcomes. Both fentanyl and morphine are controlled drugs. The Misuse of Drugs Acts, 1977 and 1984, and the Misuse of Drugs Regulations, 1988, 1993 and 2007, determine the conditions of production, possession, supply, importation and exportation of controlled drugs. Standard operating procedures (SOPs) are developed for every stage of a controlled drug’s journey from procurement (ordering, receipt and transport), safe storage, supply, administration, destruction and guidance for dealing with an incident. SOPs will be accessible to staff at all times.

#### Fentanyl and matched-placebo

Fentanyl citrate 50 μg/ml (Sublimaze, Marketing Authorisation No. PA 0748/044/001) is manufactured by Janssen Cilag, Ltd., and is an authorised product in Ireland. However, fentanyl is licensed for usage for paediatric pain via the intravenous route but not via the intranasal route. The matched size and shape of the placebo ampoule is necessary to maintain blinding of intervention by the investigators. The matched placebo for intranasal fentanyl is a 2-ml water for injection BP glass ampoule by Hamelyn Pharmaceuticals. The product is licensed in the UK for dissolving and diluting drug substances (reference no. PL 01502/0003R).

#### Morphine and matchedplacebo

Morphine sulphate 10 mg/ml BP is manufactured by Antigen Pharmaceuticals and authorised in Ireland (Marketing Authorisation No.PA 73/20/1). The matched placebo for intravenous morphine is a 1-ml water for injection glass ampoule by Roche Pharmaceuticals. It is an authorised product in Ireland for dilution of Clonazepam ampoules.

#### Overdosage considerations

In the considered event of an overdosage of opioid the approach of risk mitigation is as follows:

1. Trial pack manufacture Standard Operating Procedures;

2. Dispensing Standard Operating Procedures;

3. Monitoring of patient vital signs and clinical signs of opiate toxicity;

4. ED Staff training; and

5. Consideration of antidotal/reversal treatment (Naloxone is a standard stocked drug in the ED).

### Study procedure

#### Dose and administration schedule

The study drugs will be administered at time 0 as outlined in the study flow chart (Figure 1). The patient’s age-appropriate pain score will be recorded at time points 0, 5, 10, 15, 20, 30, 60 and 120 min by a single investigator on the patient’s case report form. After the end of the 120 min the study will be terminated. The Faces, Legs, Activity, Cry, Consolability (FLACC) scale and Manchester Pain Ruler will be used as age-appropriate pain scales for pre-verbal/early verbal children and older verbal children respectively.

**Figure 1 F1:**
[figure not shown]
**Study flow chart.** The schedule of study observations that will be recorded during the 120-min observation period.

### Outcome measures

The *primary outcome measure* is severity of pain as measured using a validated pain score at 10 min post-analgesia.

The secondary outcome measures are:

· Severity of pain as measured by pain scores at 0, 5, 15, 20, 30, 60 and 120 minutes after the administration of analgesia;

· The proportion of patients requiring rescue opioid analgesia; and

· Adverse events within the 120 minutes study period.

### Sample size, power and statistical methods

The purpose of this study is to establish non-inferiority in pain relief for IN fentanyl as compared to IV morphine in the ED treatment of severe painful sickle cell crises in children. The study is a repeated measures study, measuring pain scores before and after the treatment. A detailed statistical analysis plan has been developed in association with CSTAR. From a previous study it is estimated that the reduction in pain will be 26 mm on a visual analogue score (VAS) with a standard deviation of 6 mm [27]. As a non-inferiority study, a threshold of how different the two treatments are has to be established, generally from clinical data. A clinically meaningful difference in VAS scores has been defined as 13 mm [41,42]. Setting the allowable threshold to 50% of this limit (6 mm) and assuming the two treatments are on average equal, a sample size of 30 patients (15 per group) will provide at least 80% power to demonstrate that INF is non-inferior to IV morphine with a level of significance of 0.05.

### Data analysis

Non-inferiority of the intranasal fentanyl treatment will be established based on a repeated-measure analysis of variance (ANOVA) with time of measurement (before or after treatment) as the within-subjects factor and treatment as the between-subjects factor. Data will be analysed on an intention-to-treat and a per protocol basis.

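### The repeated-measures ANOVA named for the non-inferiority conclusion is not tied to the 6 mm margin on which the trial was sized

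*Protocol article*

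**What the plan says.** The objective, in the section Sample size, power and statistical methods, reads: "The purpose of this study is to establish non-inferiority in pain relief for IN fentanyl as compared to IV morphine". That section accepts that such a trial needs a margin ("As a non-inferiority study, a threshold of how different the two treatments are has to be established, generally from clinical data") and sets one. It starts from "A clinically meaningful difference in VAS scores has been defined as 13 mm" and continues: "Setting the allowable threshold to 50% of this limit (6 mm) and assuming the two treatments are on average equal". The planning variability is given as "the reduction in pain will be 26 mm on a visual analogue score (VAS) with a standard deviation of 6 mm". Thirty patients, 15 per group, are said to give at least 80% power at a 0.05 significance level. Whether that level is one- or two-sided is not stated.

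The primary outcome, under Outcome measures, is "severity of pain as measured using a validated pain score at 10 min post-analgesia".

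The analysis is in the Data analysis section: "Non-inferiority of the intranasal fentanyl treatment will be established based on a repeated-measure analysis of variance (ANOVA"). Time (pre versus post) is the within-patient factor and treatment the between-patient factor. The section adds: "Data will be analysed on an intention-to-treat and a per protocol basis". It mentions no margin, confidence limit, one-sided test or shifted null hypothesis. The 6 mm figure appears only in the abstract and the sample-size section. The article says that a detailed statistical analysis plan exists; it is not available here.

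**The concern.** A non-inferiority test asks whether the data exclude a deficit of 6 mm or more. The F tests of this ANOVA (treatment, and time by treatment) ask whether the data exclude a difference of zero. Neither rejecting nor retaining that second hypothesis answers the first question. The trial is therefore sized on one hypothesis, while the method named for its main conclusion, taken at face value, tests another.

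The conclusion about fentanyl is at stake. If an F test that is not significant were accepted as evidence of non-inferiority, noisier data would make the claim easier to reach. A margin-based test works the other way.

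**Working it through.** **Inputs from the protocol article:** margin 6 mm (half of 13 mm is 6.5, taken as 6); SD 6 mm for the reduction in pain; true difference 0 for power; 15 per group; level 0.05, sidedness unstated. SDs of 10 to 20 mm are my assumptions, shown as a range.

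**1. Reproducing the sample size as a margin-based test.**

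n per group = 2 × (z₁₋α + z₀.₈₀)² × SD² / margin²

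- One-sided 0.05: 2 × (1.645 + 0.842)² × 36/36 = 12.4, so 13 per group.
- One-sided 0.025: 2 × (1.960 + 0.842)² × 36/36 = 15.7, so 16 per group.

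With 15 per group, SE = 6 × √(2/15) = 2.19 mm and the noncentrality is 6/2.19 = 2.74.

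| One-sided level | Power, normal formula | Power, noncentral t, 28 df |
|---|---|---|
| 0.05 | 86.3% | 84.8% |
| 0.025 | 78.2% | 75.3% |

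The stated figure of at least 80% is therefore met at one-sided 0.05 and narrowly missed at one-sided 0.025. Either way, the calculation is that of a test against the 6 mm margin.

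**2. What the ANOVA tests.** With two times and two groups, the time-by-treatment F equals the square of the two-sample t statistic on change scores (checked on simulated data: both 0.0322). Its null is equal mean change, and 6 mm appears nowhere in it. The treatment main effect is no better suited: it averages the pre and post scores, so a difference present only after treatment enters at half its size.

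**3. Pass rates if non-significance were read as non-inferiority.** This is P(|t| < 2.048) under a noncentral t with 28 df and noncentrality (true deficit)/SE, where SE = SD × √(2/15). The 95% half-width is 2.048 × SE.

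| SD (mm) | SE (mm) | 95% half-width (mm) | Pass, true deficit 6 mm | Pass, true deficit 13 mm |
|---|---|---|---|---|
| 6 (protocol) | 2.19 | 4.5 | 24.7% | about 0% |
| 10 (assumed) | 3.65 | 7.5 | 64.5% | 7.0% |
| 12 (assumed) | 4.38 | 9.0 | 73.8% | 18.3% |
| 15 (assumed) | 5.48 | 11.2 | 81.5% | 37.0% |
| 20 (assumed) | 7.30 | 15.0 | 87.5% | 59.5% |

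A test of the confidence limit against 6 mm passes a true 6 mm deficit 5% of the time (one-sided 0.05) or 2.5% (one-sided 0.025) at every SD. It passes a true 13 mm deficit at most 0.5% of the time over this range.

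**The case against.** The strongest reply is that the Data analysis section names a model and not a decision rule. A reader might infer that the trial will declare non-inferiority whenever the ANOVA is not significant. The article does not say so. The time-by-treatment contrast is the between-group difference in change, and the same model yields its estimate, its standard error and hence a confidence limit to set against 6 mm. The preceding section sets that margin and sizes the trial with it, so the authors plainly had a margin in mind. The analysis plan that is not shown may contain the comparison. All of this stands, and the pass rates above are therefore conditional on a reading that the article permits but does not state.

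The reply does not remove the point. The sentence says how non-inferiority will be established, and the standard tests of the method it names do not address that hypothesis. This is more than a detail left out. If the analysis plan does compare a limit with 6 mm, the published sentence should say so too.

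A reader might also infer the opposite harm: a small but significant difference inside the margin being counted as failure. The planning figures do not support this. With an SD of 6 mm, significance against fentanyl needs an estimate of at least 4.5 mm. The upper 95% limit is then at least 4.5 + 4.5 = 9 mm, which fails the 6 mm criterion as well. For that limit to stay below 6 mm, the half-width would have to be under 3 mm, meaning an SD below 3/(2.048 × √(2/15)), or about 4 mm.

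Finally, the large percentages belong to assumed SDs. At the protocol's own SD, the rate is 25% for a 6 mm deficit and about zero for 13 mm.

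**Conclusion.** The point holds in a limited form. The analysis named for the primary conclusion is not linked to the 6 mm margin, and its standard F tests do not test non-inferiority. It is not established that the trial would equate non-significance with non-inferiority. If it did, the false-pass rate at a true 6 mm deficit would be about 25% at the protocol's SD, roughly five times the nominal 0.05, and 65% to 88% for assumed SDs of 10 to 20 mm.

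These rates assume 15 evaluable patients per group, normally distributed change scores with a common SD, and a two-sided 5% time-by-treatment test. The sentence governs the trial's main claim, so it should be corrected before unblinding.

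**What to change.** Replace the decision sentence in Data analysis with a rule of this kind: *Non-inferiority will be concluded only if the upper confidence limit for the intranasal fentanyl minus intravenous morphine difference in pain at 10 minutes (or the equivalent ANOVA contrast for change from baseline to 10 minutes) is below 6 mm. The result will be reported for both the intention-to-treat and per-protocol sets. ANOVA p-values play no part in this decision.*

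State the one-sided level. One-sided 0.05 (upper limit of a two-sided 90% interval) agrees with the stated power: 84.8% at SD 6 mm. One-sided 0.025 (upper limit of a two-sided 95% interval) gives 75.3% with 15 per group, so the power statement would have to be rewritten. Choose between the 10-minute score and the change contrast explicitly: the 6 mm SD is given for the reduction, and the article gives no SD for the 10-minute score itself.

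At one-sided 0.05 the cost is wording only; at 0.025 the power claim changes as well. The real downside is that the claim becomes harder to make with noisy data. With truly equal treatments and 15 per group, the chance of showing non-inferiority at one-sided 0.05 falls from 84.8% at SD 6 mm to 48.3% at an assumed SD of 10 mm and 20.0% at 20 mm.

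### The non-inferiority test rests on a before/after ANOVA with the pre-dose score as a response; a baseline-adjusted ANCOVA of the 10-minute score would match the primary endpoint and usually be more precise

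*Protocol article*

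**What the plan says.** All references are to the protocol article.

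- **Outcome measures:** the primary outcome "is severity of pain as measured using a validated pain score at 10 min post-analgesia", which is a single post-dose score. The secondary list includes "Severity of pain as measured by pain scores at 0, 5, 15, 20, 30, 60 and 120 minutes after the administration of analgesia", so the time-0 value appears among the outcomes.
- **Sample size, power and statistical methods:** the trial is sized on a change. From an earlier study, "the reduction in pain will be 26 mm on a visual analogue score (VAS) with a standard deviation of 6 mm". The margin and the assumed truth are given as "Setting the allowable threshold to 50% of this limit (6 mm) and assuming the two treatments are on average equal". Fifteen children per group are said to give at least 80% power at a significance level of 0.05; whether this is one- or two-sided is not stated.
- **Data analysis:** non-inferiority is to be shown by a repeated-measures ANOVA "with time of measurement (before or after treatment) as the within-subjects factor and treatment as the between-subjects factor". The section does not mention the time-by-treatment interaction, does not say that the post-dose measurement is the 10-minute one, and does not use the pre-dose score as a covariate.

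**The concern.** The endpoint is a 10-minute score, the sample size is built on a reduction, and the model takes the pre-dose and post-dose scores together as responses. A two-by-two model of this kind offers two terms that could carry the comparison with the margin, and they estimate different things.

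The interaction compares mean changes. It targets the right difference, but it fixes the coefficient of the baseline at 1 instead of estimating it, which usually costs precision. The treatment main effect averages each child's two scores. Treatment cannot affect the pre-dose score, so averaging dilutes any real difference. In a non-inferiority trial dilution pulls the arms together and favours the new treatment.

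At stake are some precision in a trial of 30 children and, if the wrong term were read off the output, the validity of the non-inferiority claim itself.

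**Working it through.** **Inputs from the sample size section.** n = 15 per arm; SD 6 mm, read as the SD of the change; margin 6 mm; true difference 0; alpha 0.05, taken as one-sided 0.05 and also as one-sided 0.025.

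**Assumptions not in the document.** The post-dose score is the 10-minute score; scores are on a mm scale with normal errors; the pre/post correlation r is 0.3 to 0.9; the two variances are equal, except where stated.

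**1. The plan's own figure.** SE of the difference in mean change = 6 × √(2/15) = 2.19 mm. Noncentrality = 6/2.19 = 2.74 on 28 df. Power is 84.8% at one-sided 0.05 (86.3% by the normal approximation) and 75.3% at one-sided 0.025 (78.2%). The claim of at least 80% is reproduced at one-sided 0.05.

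**2. What each term estimates.** Let δ be the true fentanyl minus morphine difference at 10 minutes. By randomisation the expected difference at time 0 is 0.

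- Treatment main effect: (0 + δ)/2 = δ/2.
- Time-by-treatment interaction: δ − 0 = δ.
- ANCOVA of the 10-minute score on treatment and time-0 score: δ.

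A simulation of 10,000 trials with δ = 6, r = 0.5 and score SD 6 gave mean estimates of 3.02, 5.98 and 6.00 mm, with SEs of 1.91, 2.18 and 1.93.

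**3. Precision of the interaction against ANCOVA.** Let b be the slope of the 10-minute score on the time-0 score and σ0 the time-0 SD. The variance of the change is the ANCOVA residual variance plus (1 − b)²σ0². With the change SD fixed at 6, the residual variance is 36 − (1 − b)²σ0². Under equal variances b = r and σ0² = 36/[2(1 − r)], so the residual variance is 36 − 18(1 − r) = 36(1 + r)/2. The change-score variance is then 2/(1 + r) times that of ANCOVA. If b = 1 (change independent of baseline), there is no gain.

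**4. Main effect against a 6 mm margin.** The SD of the mean of the two scores is σ0√[(1 + r)/2]. When δ = 6 the estimate centres on 3, which leaves 3 mm to the margin. At r = 0.5 the SD is 5.20, the SE is 5.20 × √(2/15) = 1.90, and 3/1.90 = 1.58, which gives a 45.9% chance of declaring non-inferiority.

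| r | Score SD | ANCOVA residual SD | Variance, change ÷ ANCOVA | ANCOVA power, 0.05 | ANCOVA power, 0.025 | SD of pre/post mean | False non-inferiority, main effect, 0.05 |
|---|---|---|---|---|---|---|---|
| 0.3 | 5.07 | 4.84 | 1.54 | 95.2% | 90.6% | 4.09 | 62.4% |
| 0.5 | 6.00 | 5.20 | 1.33 | 92.5% | 86.2% | 5.20 | 45.9% |
| 0.7 | 7.75 | 5.53 | 1.18 | 89.4% | 81.7% | 7.14 | 30.1% |
| 0.9 | 13.42 | 5.85 | 1.05 | 86.3% | 77.3% | 13.08 | 15.1% |

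The comparators are 84.8% and 75.3% power for the change score, and 5% for the last column.

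**5. Limits of the table.**

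- Estimating the slope costs a little. At r = 0.5 the formula SE is 1.90 and the simulated SE 1.93, about 3% more variance. At r = 0.9 this takes most of the 5% gain.
- Entry requires pain "rated 7 or greater on a 0–10 numeric pain scale or equivalent", which restricts time-0 scores but not 10-minute scores, so equal variances are only illustrative.
- With time-0 scores uniform on 70 to 100 mm and an independent change of SD 6, the slope is 1. In 20,000 simulated trials power was 84.9% for the change score and 83.7% for ANCOVA.

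**The case against.** The strongest reply is that the article already points to the harmless term. Its aim is pain relief, its sample size uses the reduction, and scores are taken before and after dosing, all of which fits the interaction. On that reading the estimate is unbiased, the SD of the change is the right input, and the power claim holds at one-sided 0.05. Under randomisation the expected difference in 10-minute scores equals the expected difference in reductions, so endpoint and sizing share an estimand. The article also says that a detailed analysis plan exists; it is not shown, and it may name the term.

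Most of this stands. It does not remove the point, because the Data analysis section itself fixes the model for the non-inferiority claim, and that model offers one term that is usually less precise and another that is biased.

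Some stronger readings do not hold:

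- **That the plan will test the halved effect.** The document does not say so, and its sizing suggests otherwise.
- **That baseline information is wasted.** The interaction uses it, with a coefficient of 1.
- **That the trial is badly underpowered because raw 10-minute scores vary more than changes.** The plan proposes no unadjusted 10-minute comparison, and its power would depend wholly on assumption: with the same inputs, about 94% at r = 0.3 and 33% at r = 0.9.
- **That listing time 0 as an outcome is an analytic error.** It is a slip of labelling; the dosing section records that score when the drugs are given, and the ANOVA treats it as pre-dose.

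**Conclusion.** The point holds in a limited form. The model does not match the 10-minute endpoint cleanly and leaves a choice of term.

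On the likelier reading, the interaction, the test is valid and reaches the stated power at one-sided 0.05, though not at one-sided 0.025 (75.3%). ANCOVA would add between nothing and about 10 percentage points at one-sided 0.05. The gain depends on a pre/post correlation that the document does not give and on equal variances; it disappears when the change is independent of baseline.

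On the less likely reading, the treatment main effect, the halving is exact and needs no assumption about correlation. A 6 mm margin would then act as 12 mm at 10 minutes, close to the 13 mm that the article calls clinically meaningful. Only the resulting error rate, 15% to 62% instead of 5%, depends on r.

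The sample size of 30 is not refuted on this account.

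**What to change.** State the primary analysis as an ANCOVA of the 10-minute score on treatment, with the time-0 score as covariate. Compare the confidence limit of the adjusted fentanyl minus morphine difference with the margin, in both the intention-to-treat and the per-protocol populations that the article already names. Label the time-0 score as baseline and take it out of the list of secondary outcomes.

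The cost is a change of wording and one degree of freedom (27 instead of 28). The baseline score is already collected and the sample size need not change. Because the article allows unblinding only after the analysis plan is agreed and the database locked, the change can be made blind.
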